### Methods for additional analyses (e.g. subgroup analyses) {20b}

The exploratory efficacy analyses will be performed at the level of the participant (mITT and PP populations) or eye (applicable to the primary outcome measure, unless otherwise specified in the SAP). Change in EDSS and neurofilament light will be analysed through linear regression. Analyses of changes in visual function and anatomy (VEP amplitude, visual acuity, colour vision, visual fields, optical coherence tomography) will use the same method as for the primary efficacy analysis.

## Methods in analysis to handle protocol non-adherence and any statistical methods to handle missing data {20c}

### Intent-to-treat (ITT) population

The ITT population is defined as all randomised participants regardless of whether they received randomised trial treatment.

#### Modified intent-to-treat (mITT) population

The mITT population is defined as all randomised participants in whom the replacement criteria were not met; that is, the duration of IMPs received being more than 2 months. The treatment group will be analysed as randomised at baseline. The unit for the primary efficacy analysis is per eye.

#### Per protocol (PP) population

The PP population is defined as those randomised participants who completed the 24 weeks of allocated treatment regardless of whether there were any dose or schedule modifications, except for participants who missed > 28 doses of either trial IMPs over the entire treatment period.

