Male participants who are unwilling or unable to use contraception during and for 3 months after the trial	Study reported preconception paternal metformin treatment is associated with major birth defects, particularly genital birth defects in boys [33]
Participants whom have received an investigational drug (including investigational vaccines) or used an invasive investigational medical device within 4 weeks before the screening assessment or is currently enrolled in an interventional investigational trial. Participants who currently use an unlicensed treatment of MS	To maximise chance that any change observed on trial is due to metformin and clemastine, rather than any other investigational product or device
Retinal nerve fibre layer thickness on spectral-domain OCT < 70 μm in the qualifying eye	Below this threshold there are severe decrements in visual function [34]; above this value implies there remain sufficient axons to remyelinate
A clinical episode of optic neuritis in the qualifying eye within the 2 years preceding screening	Following an attack of optic neuritis, VEP latencies are prolonged, but a period of recovery follows for up to 2 years [35, 36]; excluding these make improvements in latency more specific for drug-induced remyelination
Any concomitant use of oxybutynin, monoamine oxidase inhibitors (MAOIs), hypnotics or high-dose opiates	These interact with clemastine. Oxybutynin additionally has potential remyelinating efficacy (though limited blood-brain barrier penetrance)
Significant renal or liver impairment (estimated glomerular filtration rate (eGFR) < 60 mL/min/1.73 m^2^; alanine aminotransferase > 3 times the upper limit of normal)	Metformin very rarely can cause liver dysfunction and the incidence of lactic acidosis rises with impaired renal function
People taking medication for diabetes mellitus	Metformin would alter glycaemic control
People with a diagnosis of epilepsy	Clemastine contraindicated in epilepsy. VEP testing contraindicated in photosensitive epilepsy
Concurrent use of 4-aminopyridine or fampridine	These can improve VEP and saccadic latency [37, 38]
History of prostatic hypertrophy, significant cardiac conduction block, decompensated heart failure, stenosing peptic ulcer, or pyloroduodenal ulceration	Clemastine contraindicated in these conditions

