### Criteria for discontinuing or modifying allocated interventions {11b}

If adverse events (AEs) occur that are attributable to metformin—most likely gastrointestinal side effects—the trial team may reduce or stop the metformin dose. If symptoms settle, then the dose may be increased again, at the discretion of the trial doctor. In the event of an unrelated illness, such as diarrhoea and vomiting requiring hospitalisation or a requirement for surgery, then both IMPs should be temporarily discontinued. Additionally, the development of deranged liver function (ALT greater than 3 times the upper limit of normal) or renal function (eGFR < 60 mL/min/1.73 m^2^) during the course of the trial would prompt a repeat blood test and suspension of all IMPs for at least 1 week. No dose modifications are permitted for clemastine.

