## Statistical methods

### Statistical methods for primary and secondary outcomes {20a}

A detailed statistical analysis plan (SAP version 1.0 (14 January 2025)) provides an account of the statistical methods for analysing the trial. Primary efficacy analyses will be based on the modified intent-to-treat (mITT) population with supplementary analyses with the PP population (definitions Sect. 20c).

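### The per-protocol definition has no test for prohibited VEP-altering drugs, and does not say whether a team-directed metformin stop counts as missed doses

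*Protocol article*

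**What the plan says.** Section {20c}, Per protocol (PP) population, requires that a randomised participant finished the allocated 24-week course, and applies this "regardless of whether there were any dose or schedule modifications, except for participants who missed > 28 doses of either trial IMPs", counted across the whole course. It is worded as a complete definition and does not point to a further list of deviations. Section {20a} gives the set its role: the primary efficacy analysis uses the mITT population, with "supplementary analyses with the PP population".

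Three other sections bear on who should be in the set.

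- **Prohibited drugs.** Section {11d} prohibits fampridine and 4-aminopyridine, among others, during the trial, and has all concomitant medication recorded in the CRF. Table 1 in section {10} excludes current users at entry for this reason: "These can improve VEP and saccadic latency".
- **Stopping one drug.** Section {11b} says that for adverse events attributable to metformin "the trial team may reduce or stop the metformin dose". For the other drug, "No dose modifications are permitted for clemastine".
- **Counting doses.** Section {11c} sets up a dosing diary and pill count. A cumulative 28 missed doses, equated there with 14 days, triggers review by the chief investigator.

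**The concern.** A per-protocol analysis is meant to show the result among participants who followed the protocol in the respects that matter for the endpoint. The article itself names two drugs that change P100 latency and bans them on trial. The section on the primary outcome ({12}) also places the final VEP two weeks after treatment ends, so that a direct drug effect on conduction cannot be mistaken for remyelination. The PP definition does not carry that protection forward. A participant who starts a banned conduction-altering drug remains in the set, and the drug acts in the same direction as the hoped-for treatment effect.

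The second difficulty is that membership cannot always be determined. If the team stops metformin and clemastine continues, one clause of the definition points towards keeping the participant and two point towards removing them. Left open, the choice could be made after results are known.

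**Working it through.** **1. The plan's own sample-size figure.** Inputs from section {14}: difference 3.0 ms, SD 5 ms, two-sided 5%, 80% power. The normal approximation gives n = 2 × (1.96 + 0.84)² × 5² / 3.0² ≈ 43.6, so 44 eyes per arm. The two-sample t-test gives 44.6, so 45, with 80.4% power at 45. Then 45 / 0.90 = 50. The stated 45 and 50 reproduce. Like the plan, this treats eyes as independent.

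**2. The definition applied to three participants.**

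| Participant | Completed 24 weeks? | More than 28 missed doses of either IMP? | In PP? |
|---|---|---|---|
| Took all IMP; used fampridine on trial | Yes | No | Yes: no clause removes them |
| Metformin reduced for tolerability, both IMPs continued | Yes | No | Yes: modifications are disregarded |
| Metformin stopped by the team at week 12, clemastine continued | Unclear | Unclear | Depends on the reading |

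The first row is the clear gap. The second is coherent, because section {8} describes the regimen as the maximally tolerated metformin dose. The third is the ambiguity.

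**3. Size of the prohibited-drug gap.** The documents give neither a frequency of use nor a latency change, so both are assumptions. If k eyes in an arm of 45 each shorten by d ms because of the drug, the arm mean moves by k × d / 45:

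- k = 1, d = 3: 3/45 = 0.07 ms (2% of 3.0 ms)
- k = 1, d = 10: 10/45 = 0.22 ms (7%)
- k = 2 (both eyes of one participant), d = 10: 20/45 = 0.44 ms (15%)

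In the active arm this enlarges the apparent benefit; in the placebo arm it shrinks it.

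**4. Size of the dose-counting ambiguity.** Twice daily for 24 weeks is 24 × 7 × 2 = 336 dosing occasions per IMP. The limit of 28 is 28/336 = 8.3%, or 14 days. A stop at week w omits (24 − w) × 14 doses:

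| Stop at week | Doses omitted | If counted as missed | If treated as a modification |
|---|---|---|---|
| 12 | 168 | Excluded | May be kept |
| 20 | 56 | Excluded | May be kept |
| 22 | 28 | Kept (not above 28) | May be kept |

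Section {11a} gives 5% discontinuation for metformin in general use. With about 35 active participants (70 randomised 1:1), 0.05 × 35 = 1.75, or roughly two people.

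If a fraction f of active-arm eyes in PP had stopped metformin and showed no effect at all, the difference would be 3.0 × (1 − f). Power is from the t-test with 45 eyes per arm and SD 5 ms:

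| f | Difference | Power |
|---|---|---|
| 0 | 3.00 ms | 80% |
| 5% | 2.85 ms | 76% |
| 10% (assumed) | 2.70 ms | 72% |
| 20% (assumed) | 2.40 ms | 62% |

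If those eyes kept half the effect, 5% stopping gives 2.93 ms and 78%. Section {11a} reports 3.2 ms for clemastine alone in the earlier crossover trial, so zero residual effect is a pessimistic assumption.

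**The case against.** **The SAP may hold a fuller deviation list.** It is not shown, and an article may leave detail to it. This has some weight, but the article states its two tests as the definition, and the definition as stated keeps users of prohibited drugs.

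**Use of these drugs should be rare.** They are excluded at entry, prohibited on trial and recorded. That stands. It limits the likely size, and it also makes the exclusion easy to apply.

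**Stopped metformin may already be covered.** A reader might infer that PP definitely keeps participants who received clemastine alone for most of the trial. The text does not support that. Completing allocated treatment can be read as completing both drugs, and the limit on missed doses applies to either IMP, which suits non-receipt of one drug. Only the instruction to disregard modifications points the other way. What stands is that the wording is unresolved.

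**On-trial optic neuritis.** A reader might also infer that PP should drop eyes with optic neuritis after baseline, since Table 1 excludes recent episodes and says "excluding these make improvements in latency more specific for drug-induced remyelination". That rationale concerns natural recovery after an attack before entry. A new attack is a post-randomisation event, not non-adherence. Section {11a} reports fewer new or enlarging T2 lesions with metformin, so such events may depend on treatment, and removing them could bias the comparison. One eye prolonged by an assumed 10, 20 or 40 ms would move a 45-eye arm mean by 0.22, 0.44 or 0.89 ms. That may justify a sensitivity analysis, but not a PP exclusion.

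**Conclusion.** The point holds in limited form. As written, the PP set retains participants who took fampridine or 4-aminopyridine against the protocol, although the article says these drugs can improve the primary measure. Whether a team-directed metformin stop removes a participant cannot be determined from sections {11b}, {11c} and {20c} together.

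It would be tempting to conclude that the PP analysis cannot support a combination effect, or that its agreement with mITT would be uninformative. The documents do not support that. PP is supplementary, and the amount of contamination is unknown. At the article's general 5% metformin discontinuation rate, with no residual effect assumed, dilution is 3.00 − 2.85 = 0.15 ms and about 4 points of power. The prohibited-drug figures (0.07 to 0.44 ms for one participant) rest wholly on assumed latency changes and an assumed single user. The primary mITT analysis is not affected by how the PP set is defined.

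**What to change.** 1. Add to the PP definition: exclude participants who took fampridine or 4-aminopyridine at any time between baseline and the week 26 VEP, identified from the concomitant-medication record in the CRF.
2. Reconcile sections {11b}, {11c} and {20c} by stating whether doses omitted after a team-directed metformin stop count towards the 28-dose limit. Also align the review trigger (28 missed doses) with the exclusion limit (more than 28), or say that the difference is intended.
3. Do not make on-trial optic neuritis a PP exclusion. If it is addressed, use a separate sensitivity analysis that omits the affected eyes.
4. Leave the mITT population unchanged on these points.

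Make these decisions blind to allocation. The Trial status section planned analysis from April 2025, so if unblinding has occurred, label the revised PP set post hoc and report it beside the set as published. The cost is a few lines of SAP wording and a slightly smaller PP set; item 1 needs no new data.

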#### Safety population

The safety population comprises all participants who were randomised and received any dose of trial treatment.

#### Missing data

Missing data related to the primary outcome measure will be rare and will be accounted for using the mixed-effects models in the analyses. No imputation will be made for missing data.

#### Plans to give access to the full protocol, participant-level data and statistical code {31c}

Ownership of the data arising from this trial resides with the trial team. The CI will have full access to the final data set following completion of the analysis by the trial statistician. The protocol, statistical analysis plan and the deidentified dataset for the primary and secondary outcomes (with corresponding statistical codes) will be made available with publication from the Cambridge Clinical MS Research Group’s website (temporary web address at time of submission: https://www.cambridgeclinicalmsresearch.com/). Access requests should be made to the CI ([name]: [contact]). A signed data access agreement will be required, and investigator support might be provided if part of an academic collaboration.

## Oversight and monitoring

### Composition of the coordinating centre and trial steering committee {5d}

The trial management group will run the trial day to day, and its members include CCMR Two investigators, trial coordinators, data managers, the trial statistician, and trial pharmacist. The TMG will meet monthly. Coordination and data management are performed by the neuroscience theme of the Cambridge Clinical Trials Unit.

Overall supervision of the trial will rest with the TSC. The TSC will consist of an independent Chairperson, independent physician experts, and an independent statistician, as well as representatives of the Sponsor and funder. The TSC will meet at least once a year and receive reports from TMG and IDMC. The charter details the operation of the TSC.

### Composition of the data monitoring committee, its role and reporting structure {21a}

The IDMC is independent of trial investigators, Sponsor and funder. The composition of the IDMC will be defined in the IDMC charter. The IDMC will meet at least every 12 months and will review the accumulated unblinded trial data for participant safety, trial conduct and progress, and it will make recommendations to the TSC concerning the continuation, modification, or termination of the trial. In addition, the IDMC will be asked to review the assumptions used in the sample size estimation when 20 patients have had their efficacy endpoints assessed, and advise whether a sample size re-estimation should be considered (see sample size, Sect. 14).

### Adverse event reporting and harms {22}

Recording of all AEs will start from the point of informed consent regardless of whether a participant has yet received a medicinal product. All AEs will be reported using MedDRA terminology version 24. Individual AEs will be evaluated by the investigator. This includes the evaluation of its seriousness and any relationship with the IMP(s). Expectedness will be assessed against the latest MHRA approved version of the reference safety information (RSI). Serious adverse events (SAEs) will be assessed by the CI in terms of expectedness and relatedness. SAEs are then notified to the Sponsor within 24 h of first notification. Suspected unexpected serious adverse reactions (SUSARs) will be subject to expedited reporting to the Sponsor, REC, and competent authority (MHRA), as detailed in the trial protocol.

### Frequency and plans for auditing trial conduct {23}

The investigator will make all trial documentation and related records available should an MHRA Inspection occur. Should a monitoring visit or audit be requested, the investigator will make the trial documentation and source data available to the Sponsor’s representative. All participant data will be handled and treated confidentially. The monitoring frequency is determined by an initial risk assessment prior to the start of the trial and a plan generated detailing the frequency and scope of monitoring for the trial.

### Plans for communicating important protocol amendments to relevant parties (e.g. trial participants, ethical committees) {25}

Protocol amendments will be reviewed and agreement received from the Sponsor for all proposed amendments prior to submission to the Health Research Authority (HRA), Research Ethics Committee (REC) and/or MHRA. The CI is responsible for communicating important protocol modifications to investigators, trial participants, registries and regulators. Before the start of the trial, we obtained ethical approval from the East Midlands—Nottingham 2 Research Ethics Committee (21/EM/0120).

### Dissemination plans {31a}

The results of the trial will be released either at oral presentation or trial publication, after a dissemination plan is agreed with the TSC. Summaries of results will also be made available to participants by means of a newsletter (communicated by email) and by means of an informal meeting with the trial team (virtual and in-person options available). Authorship decisions will be guided by uniform requirements for manuscripts submitted to medical journals (www.icmje.org).

## Discussion

While several clinical trials have deployed drugs capable of enhancing the differentiation of the OPC [23, 24, 26], the demonstration that metformin can reverse age-related changes in OPCs that prevent them from responding to such factors is an important development [30]. Consequently, there is a compelling rationale to test metformin, alongside pro-differentiation agents such as clemastine, in clinical trials of people with MS.

CCMR Two will test the hypothesis that metformin and clemastine can enhance remyelination in people with MS using both visual evoked potentials and magnetisation transfer ratio imaging; it is anticipated that in this way we will be able to detect the functional and structural consequences of remyelination with a sample size feasible for a single centre trial. We have applied our experience from the CCMR One trial—which showed that lesion remyelination in response to RXR agonism was dependent on its location and baseline tissue integrity[27]—and optimised our analyses to be sensitive to remyelination in those lesions that are more demyelinated at baseline and those that are located in the grey matter. We have additionally introduced selection criteria to yield a cohort that we expect is most likely to have a measurable between-group response in this trial setting.

There are, however, limitations to our chosen trial design. A particular challenge to translating promising preclinical research into remyelination trials is uncertainty about the optimum outcome measures to employ [73]. Our approach for CCMR Two has been to prioritise the VEP, given it has been directly confirmed to reflect myelin status in chronically demyelinated optic nerves [74] and has shown significant effects in three previous clinical trials [23, 24, 27], but to also include the MTR analyses that we think will be most sensitive to remyelination; in CCMR One, perhaps the most compelling evidence of a biological effect of bexarotene was the alignment between the imaging and electrophysiological results. We have also included several techniques that might be sensitive to, or represent the downstream consequences of, remyelination: MF-VEP [52], OCT [34], saccadometry [65], and LCLA [75]. Ultimately, all outcome measures in this field are exploratory, and several of this trial’s limitations stem from this point. In particular, in selecting only relapsing-remitting patients with visual pathway demyelination and focusing on remyelination of this particular tract, there follow uncertainties about the generalisability of results to the wider MS population. An additional limitation is the interpretation of a positive result. Would the primary effect be primarily attributable to the action of metformin, clemastine, or is there evidence of synergy between the two? There are pro-differentiation factors already present in demyelinated lesions [76] and metformin alone might be sufficient to achieve remyelination. Meanwhile, the modest effect on the VEP latency seen in the trial might indicate a mild pro-differentiation effect that can be better ‘unlocked’ by co-administration of metformin. CCMR Two is not designed to test these questions; the objective is to see if the remyelinating effect seen in animals translates into humans. Dissecting the different contributions of each drug and interrogating the possibility of synergy would require a much larger trial, demanding a multi-centre design, which would pose a particular challenge to using electrophysiological outcome measures [28, 73]. Questions would also remain as to how to deploy a remyelination treatment, such as whether it should be given continuously or periodically.

Despite this, CCMR Two represents an important step towards identifying a treatment capable of directly protecting neurons from degeneration, outside of the indirect effects of immunomodulatory disease-modifying treatments. As these drugs are widely used and known to be safe, this approach could then be readily deployed in confirmatory and phase 3 trials. If no treatment effects are shown, we are confident that the trial will have legacies that will lead to improvements in trial design and the development of optimum outcome measures.

## Trial status

Trial protocol 5.1, 27 March 2024. Statistical analysis plan 1.0, 14 January 2025. Recruitment began in March 2022 and was completed in October 2024. The trial is still ongoing at the time of submission, and analysis will begin in April 2025. The protocol paper was submitted for publication in March 2025 after recruitment closed, but this was to allow for the incorporation of the statistical analysis plan, which remained under revision until January 2025.

## Data Availability

The protocol, statistical analysis plan and the deidentified dataset for the primary and secondary outcomes (with corresponding statistical codes) will be made available with publication from the Cambridge Clinical MS Research Group’s website (temporary address at time of submission: https://www.cambridgeclinicalmsresearch.com/). Access requests should be made to the chief investigator ([name]: [contact]). A signed data access agreement will be required, and investigator support might be provided if part of an academic collaboration.

